#### Data management

In the ICE-COVID trial, data collection is performed by trained local research staff and data entry in the REDCap database is completed contemporaneously and in a standardised fashion across two research locations in Swansea, UK. Data will be monitored via an independent data monitoring committee (DMC) using a weekly report to assess compliance with the completion of the daily symptom tracker questionnaire and identify symptomatic participants.

### Data access

Only members of the direct research team will have access to participant identifiable data. To ensure the confidentiality of samples, participants will be assigned a study identifier code which will be used to analyse data not performed at the research sites. No data will be transferred outside of the EU. Access to the system will be available for inspectors and sponsor representatives (monitors/auditors) this will enable source data verification of clinical trial subjects whilst protecting the confidentiality of non-trial patients

#### End of study treatment

Participants will be invited for an end-of-study visit and asked to bring back the empty spray bottles to be weighed as an additional measure of compliance. Participants will be asked to complete an end-of-study quality-of-life questionnaire: EQ-5D-3L, usability questionnaire as well as adverse events reporting. Participants will also undergo study exit blood tests which will include SARS-CoV2 serology.

### Ancillary and post-trial care

There is no anticipated harm and compensation for trial participation.

### Sample size and rationale for non-inferiority

We calculated the sample size based on the primary outcome measures (having COVID-19) and the respective assumed effect size in relation to the intervention (receiving iota-carrageenan spray) and the placebo nasal spray (0.5% saline). The magnitude of any effect of the nasal and throat spray on COVID-19 symptoms is unknown. However, 20.2% of healthcare professionals reported at least one symptom associated with SARS-CoV2 infection during the first wave of the pandemic, with a twelvefold increase in the risk of a positive test compared to the general population [4]. It has been recognised that key workers have been disproportionately affected by COVID-19 infections and the overall seroprevalence of SARS-CoV-2 antibodies has been found to be 24.4% in healthcare professionals [52, 53]. .Assuming an expected difference of 12.5% (i.e., 25% and 12.5% in the intervention and control group respectively), a sample of 304 participants (i.e. 152 in each arm) will provide 80% statistical power using a two-sided significance level of 5%. Assuming a lost to follow-up of 20%, a total of 380 participants (190 in each arm) will be needed.

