#### Seroconversion

Participants will be tested for SARS-CoV-2 antibodies using the enzyme-linked immunosorbent assay at the start and end of the study period. The presence of SARS-CoV-2 antibodies at the start of the trial indicates the previous infection with COVID-19 and the participant data will as such be excluded from the trial. Participants will be deemed to have acquired COVID-19 during the study period if they are antibody negative at the start of the study and positive for SARS-CoV-2 antibodies at the end of the study (i.e. seroconversion). This will be an essential means of detecting individuals with asymptomatic infection during the study period.

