### Dissemination

The aim of this trial is to report definitive results regarding the effectiveness of carrageenan nasal and throat spray in protecting key workers from infection with SARS-Cov2. Dissemination of the outputs from this trial is proposed through depositing information in open access repositories prior to publication in a high-impact, open access journal and by a presentation at relevant international conferences. Given the urgency and unprecedented nature of the current situation, we will use every means available to us to ensure the results are disseminated rapidly, efficiently and effectively.

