### Revision to trial design

The trial protocol was written prior to the introduction of vaccines and was initially aimed to recruit healthcare professionals who have not been previously tested positive for COVID-19. However, the success of the UK vaccination programme and prioritisation of healthcare professionals for vaccines has meant that the majority of staff were no longer eligible for the trial. Approval was therefore sought from the Sponsor (Swansea University), REC and SBUHB (NHS) R&D Office to widen the potential pool of study participants to include all key workers or those needing to interact with people outside of their household for study or work from the 11th of January 2021. The full trial protocol is available on ClinicalTrials.gov [40].

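### The 80% power is not supported for the trial as run: the 25% risk appears to come from a healthcare-worker seroprevalence, not a 10-week incidence in seronegative participants of the widened population

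*Protocol article*

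**What the plan says.** In the protocol article, the section *Sample size and rationale for non-inferiority* says that the size of any effect on symptoms is unknown. It then gives two background rates, both in healthcare professionals. One is 20.2% with at least one symptom in the first wave, "with a twelvefold increase in the risk of a positive test compared to the general population". The other is that "the overall seroprevalence of SARS-CoV-2 antibodies has been found to be 24.4% in healthcare professionals". The calculation follows directly: "Assuming an expected difference of 12.5% (i.e., 25% and 12.5% in the intervention and control group respectively"). The number required is "a sample of 304 participants (i.e. 152 in each arm"), and the article says that this size "will provide 80% statistical power using a two-sided significance level of 5" per cent. Allowing 20% loss to follow-up brings the total to 380.

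Other sections fix what is counted, in whom and for how long:

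- *Primary outcome* under *Outcomes*: infection acquired during the study, shown by PCR at symptom onset or by seroconversion.
- *Seroconversion*: "The presence of SARS-CoV-2 antibodies at the start of the trial indicates the previous infection", and those participants' data are excluded.
- *Abstract*, methods paragraph, and *Quality of life data*: 8 weeks of spray, 10 weeks of symptom tracking, study end at week 10.
- *Revision to trial design*: recruitment was first aimed at healthcare professionals. From 11 January 2021 approval was sought for a broader intake: "widen the potential pool of study participants to include all key workers or those needing to interact with people outside of their household", whether that contact comes through study or through work. No new event rate, sample size or power accompanies the change.
- *Dissemination*: "The aim of this trial is to report definitive results regarding the effectiveness of carrageenan nasal and throat spray".

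**The concern.** A seroprevalence counts everyone infected at any time up to the survey. The trial counts new infections in about 10 weeks among people with no antibodies at the start. The two agree only if the whole prevalence built up in a period about as long as the follow-up, and if the enrolled population is infected as fast as the surveyed one. The article supports neither condition, and the population has since been widened beyond the group surveyed.

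Power for a binary outcome at a fixed relative effect falls quickly as the control risk falls. If the 10-week risk is well below 25%, 380 participants could detect only very large effects, and a null result could be misread as evidence of no effect. That risk is greater because the article promises definitive results.

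**Working it through.** **Inputs.** From the sample size section: risks of 25% and 12.5%, two-sided 5%, 80% power, 152 per arm evaluable, 20% loss. From *Randomisation*: 1:1 allocation. As printed, 25% belongs to the intervention arm and 12.5% to control. For a prevention trial these labels must be reversed, so 25% is read here as the control risk. The two-sided sample size is the same either way.

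**Reproducing the plan's figure.** Two proportions, pooled variance under the null, no continuity correction, with p̄ = (p1 + p2)/2:

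n per arm = [1.960·√(2p̄(1−p̄)) + 0.842·√(p1(1−p1) + p2(1−p2))]² / (p1−p2)²

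With p1 = 0.25, p2 = 0.125 and p̄ = 0.1875, this is (1.0819 + 0.4586)² / 0.015625 = 151.9. That gives 152 per arm and 304 in total, and 304/0.8 = 380. Power at 152 per arm is 80.0%. The stated numbers follow from the stated inputs.

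**Power at other control risks.** Same formula solved for power, n = 152 per arm, relative risk 0.5:

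Power = Φ{ [(p1−p2)·√n − 1.960·√(2p̄(1−p̄))] / √(p1(1−p1) + p2(1−p2)) }

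For 10% against 5%: (0.6164 − 0.7301)/0.3708 = −0.306, and Φ(−0.306) = 38.0%.

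| Control risk | Basis | Power |
|---|---|---|
| 25% | plan's assumption | 80.0% |
| 24.4% | the seroprevalence, taken as if it were a 10-week risk | 78.8% |
| 20.2% | the symptom rate, taken as if it were a 10-week risk | 69.2% |
| 15% | assumed | 54.4% |
| 10% | assumed | 38.0% |
| 5% | assumed | 20.8% |

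**Smallest effect detectable with 80% power at 152 per arm.** The relative risk must be about 0.44 at a control risk of 20%, 0.36 at 15% and 0.23 at 10%. At 5%, no effect reaches 80% by this formula.

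**Why the window behind the 24.4% matters.** The article does not give it. If the infections accrued at a constant rate over W weeks (an assumption), the 10-week risk is 1 − (1 − 0.244)^(10/W). W = 10 gives 24.4% and 79% power. W = 13 gives 19.4% and 67%. W = 26 gives 10.2% and 39%. These figures also assume that the widened population is infected at the healthcare workers' rate.

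**Exclusion of baseline seropositives.** The step from 304 to 380 covers loss to follow-up only. If 10% of those randomised are also excluded for antibodies at entry (assumed), 190 × 0.9 × 0.8 = 136.8 per arm remain, and power at 25% against 12.5% is 75.7%. At 5% excluded it is 78.0%. Exclusion does not by itself lower the risk among those who stay; it reduces how many can be analysed.

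**The case against.** The strongest reply is that the article only says it assumes 25%. It never says that this figure was taken from the 24.4%. That is correct: the link is an inference from adjacent sentences, though no other source is offered.

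A short accrual window also cannot be ruled out. If the 24.4% built up in about 10 weeks at a rate that the enrolled population shares, power is 79%, close to the claim. So a reader might infer that 380 participants will fail to give 80% power, but the documents do not establish that. They contain neither the true 10-week incidence nor the survey window.

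A reader might also divide 25% by the article's factor of twelve to get a risk for the widened population. That does not hold. The factor compares healthcare staff with the general population on the risk of a positive test. Entry was widened to key workers and people who mix outside the household, and the same section says key workers were disproportionately affected.

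Nor can one say that the calculation was never redone. This article reports no revision, but it refers to a fuller protocol elsewhere.

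Finally, power need not fall if the 12.5-point difference is kept: 20% against 7.5% gives 89%. That is a relative risk of 0.375 (7.5/20) rather than 0.5, and the article gives no support for so large an effect.

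These replies limit the claim to one of missing support. None of them supplies a basis for 25% as a 10-week risk.

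**Conclusion.** The concern holds in this form: 80% power is not shown to apply to the trial as run. The arithmetic is right, but the 25% that drives it is unsupported as a 10-week risk of new infection in seronegative participants of the widened population.

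The size of the shortfall is conditional. For a halving of risk with 152 evaluable per arm, 80% power requires a control risk of at least about 25%. Below that, power drops steeply, to roughly half the stated value at a 10% control risk and a quarter of it at 5%. Excluding baseline seropositives costs a few further points even if 25% is right. These results rest on the two-proportion formula that reproduces the plan's own number, on a fixed relative risk of 0.5, and on an assumed range of control risks.

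**What to change.** In *Sample size and rationale for non-inferiority*:

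1. Replace the seroprevalence with an assumed 10-week incidence of the primary outcome in seronegative participants of the current population, and give its source.
2. Keep 380. Add a short table of its power, and of the smallest relative risk detectable with 80% power, for control risks from, for example, 5% to 25%. Make clear whether the 20% allowance also covers participants excluded for antibodies at entry.
3. State that, for a halving of risk, 80% power requires a control risk of at least about 25%.
4. Correct the arm labels, which as printed give the higher risk to the intervention arm.

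In *Dissemination*, tie the promise of definitive results to the width of the confidence interval, so that a null result is read against the effects it does and does not exclude.

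The cost is a few sentences and one small table. No extra participants are needed. The stated power will look less favourable unless a 10-week control risk near 25% can be justified.

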### Statistical analysis

Data will be analysed in accordance with an intention-to-treat analysis. Each of the outcome measures will be checked for the distribution to be normal. Each of the outcome measures and important baseline covariates would be reported along with their missingness. If required appropriate imputation method would be adopted in the main analysis. All the statistical data management and analysis will be done under standard statistical software (e.g. STATA version 16 or IBM SPSS version 26).

#### Primary outcome

The primary outcome measure is a binary variable whether COVID-19 infection has been confirmed by PCR swab or not. We will perform a summary analysis reporting the outcome of the categories of two trial arms with respect to the primary outcome measure. The odds ratio and related statistical significance of the chi-square test will be reported. Following on, an adjusted analysis will be done adopting a logistic regression model. The adjustment would be done using the baseline covariates like demographics, co-morbidities (especially history of COVID-19), current medications along with baseline QoLs. The selections of the covariates would be done based on literature reviews along with discussing with the clinical co-applicants involved in this trial. This will also depend on the missing of the covariates and the selection procedure in the statistical modelling.

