Carrageenan covers a range of sulphated polysaccharides and oligosaccharides extracted from red edible seaweed. It is widely used to thicken, emulsify, and preserve food and drink, as a vegetarian and vegan alternative to gelatin, as well as in the cosmetic and pharmaceutical industry. The three commercially important carrageenans are iota-, kappa- and lambda- carrageenans, which consist of disaccharide repeating units with one, two and three sulphate ester groups respectively [20]. The in vitro antiviral activity of carrageenan was first described in 1958 when carrageenan was shown to exert a marked inhibitory effect on the growth of influenza B virus and mumps virus in embryonated chicken eggs [21]. Since then, carrageenan has shown in vitro anti-viral efficacy against a wide range of viruses [22–32]. Recently, it has been demonstrated to have in vitro antiviral activity against the novel SARS-CoV-2 [33]. In vivo clinical trial data has previously demonstrated the benefit of iota-carrageenan nasal spray in reducing the duration of symptoms of the common cold, as well as the viral load in nasal lavage, compared with saline placebo sprays [34–38]. The mechanism of action is believed to be one of preventing the binding and entry of viral particles into nasal epithelial cells [22]. In order to cause infection respiratory viruses must reach their specific host cell surface receptor by moving through respiratory fluid and mucus (10 μm depth) without any means of self-propulsion [39]. Initially, this depends on Brownian motion and eventually the positively charged virus comes close enough to the cell to be attracted via large negatively charged molecules on the cell surface known as Heparan Sulphate (HS) Proteoglycans [40]. It is thought that Carrageenan mimics the HS and can, therefore, trap the virus and prevent infection of adjacent epithelial cells [35]. Carrageenan trapped viruses are thought to be transported by mucociliary clearance to the nasopharynx, swallowed, and then destroyed in stomach acid.

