### Outcomes

#### Primary outcome

Acquisition of COVID-19 infection as confirmed by a positive PCR swab taken at symptom onset or seroconversion during the study

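### The analysis section codes the primary outcome as PCR-confirmed or not, while the outcome definition counts a positive PCR or seroconversion; the two must be reconciled

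*Protocol article*

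**What the plan says.** In the protocol article, the Primary outcome entry under Outcomes reads: "Acquisition of COVID-19 infection as confirmed by a positive PCR swab taken at symptom onset or seroconversion during the study". The Abstract gives the same definition.

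The Seroconversion section makes the second route operational: "Participants will be deemed to have acquired COVID-19 during the study period if they are antibody negative at the start of the study" and antibody positive at the end. Of this serology it says: "This will be an essential means of detecting individuals with asymptomatic infection during the study period".

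The Primary outcome entry under Statistical analysis states a different variable: "The primary outcome measure is a binary variable whether COVID-19 infection has been confirmed by PCR swab or not". Seroconversion is not mentioned there. The chi-square test, odds ratio and adjusted logistic model described in that entry all act on this variable.

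The sample size section says "We calculated the sample size based on the primary outcome measures (having COVID-19"), uses rates of 25% and 12.5%, and shortly before that reports that "the overall seroprevalence of SARS-CoV-2 antibodies has been found to be 24.4% in healthcare professionals".

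**The concern.** Two analysts working from this article could build two different primary variables. One would count a participant who is antibody negative at entry, never swabbed positive and antibody positive at exit as a case; the other would count the same person as uninfected. Nothing in the article says which governs, so the choice could be made after the results are known.

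The choice changes the question. The primary objective concerns the risk of COVID-19. Swabs are taken at symptom onset, so a PCR-only variable measures infection that produced symptoms and then tested positive. The Hypothesis section proposes that the spray may either prevent infection or lessen the severity of infections that do occur. If only the second were true, fewer participants on the spray might reach a swab, and a PCR-only comparison could show fewer cases with no infection prevented. Counting seroconversion is the plan's own safeguard against this, and the analysis entry leaves it out.

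**Working it through.** **Inputs from the article.** Rates 25% and 12.5%; two-sided 5%; 80% power; 152 per arm (304); 20% loss, giving 190 per arm (380). The printed text attaches 25% to the intervention arm. I take 25% as the placebo rate; the labels do not affect a two-sided sample size.

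**Input not in the article.** The share of infections that symptom-triggered PCR would detect. Every detection share below is an assumption.

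**Formula.** Comparison of two proportions, pooled variance under the null, no continuity correction. With p1 on placebo, p2 on spray, p̄ their mean and n per arm:

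power = Φ{ [ (p1 − p2)√n − 1.96·√(2p̄(1 − p̄)) ] / √(p1(1 − p1) + p2(1 − p2)) }

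**Step 1: the plan's own figure.** p̄ = 0.1875, and the two square-root terms are 0.552 and 0.545.

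- Required n = (1.96 × 0.552 + 0.842 × 0.545)² / 0.125² = 151.9, rounded up to 152 per arm.
- Power at 152 = Φ(0.843) = 80.0%.
- 304 / (1 − 0.20) = 380.

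All stated figures reproduce, for an endpoint with rates of 25% and 12.5%.

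**Step 2: PCR only, equal share missed in both arms.** Both rates are multiplied by the detected share; the risk ratio stays at 0.5.

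| Missed in both arms | Observed rates | Power at 152 per arm | n per arm for 80% |
|---|---|---|---|
| 0% | 25% v 12.5% | 80.0% | 152 |
| 10% | 22.5% v 11.25% | 74.7% | 173 |
| 20% | 20% v 10% | 68.7% | 199 |
| 40% | 15% v 7.5% | 54.4% | 278 |
| 50% | 12.5% v 6.25% | 46.4% | 341 |

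If nobody were lost and all 190 per arm were evaluable, power with 20% missed would be 78.2%.

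**Step 3: PCR only, the spray works and detection is lower on it.**

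- Detection 80% placebo, 60% spray: 0.25 × 0.8 = 20% v 0.125 × 0.6 = 7.5%; power 89.0%.
- Detection 60% placebo, 40% spray: 15% v 5%; power 83.1%.

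Power does not fall here, but part of the observed difference is a difference in detection.

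**Step 4: PCR only, no true effect on infection (25% in both arms), detection lower on the spray.** The same formula gives the chance of a significant result in the spray's favour.

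- Detection 80% placebo, 70% spray: 20% v 17.5% observed; Φ(−1.40) = 8.0%.
- Detection 60% placebo, 40% spray: 15% v 10% observed; Φ(−0.64) = 26.0%.

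The nominal one-directional rate is 2.5%.

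**The case against.** The best reply is that the intent is plain. The Seroconversion section says outright that seroconverters count as having acquired COVID-19, and the analysis entry never says they are non-cases, so its wording may be loose shorthand. That is fair as a reading of intent, and it is why the consequences here are conditional on literal application. It does not remove the conflict: the analysis entry states a definition, and that definition is not the one under Outcomes.

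A reader might infer that the trial has lost its 80% power. The documents do not support that. They give no share of infections found by serology alone, and the fall in step 2 needs an equal missed share in both arms. The false-positive argument in step 4 needs lower detection on the spray, and under that condition with a working spray power can rise (step 3). The two harms are alternatives and should not be added together.

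A reader might also infer that the article says the spray will make swabs less sensitive. It does not. The sentence reporting lower viral load, "as well as the viral load in nasal lavage, compared with saline placebo sprays", concerns common-cold trials of a nasal spray; for SARS-CoV-2 the Introduction reports only in vitro activity, and reduced severity is a hypothesis. Differential detection is therefore plausible, not stated.

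Nor is the 25% shown to come from seroprevalence. The sample size section also cites a 20.2% symptom figure and a twelvefold risk of a positive test, and derives the 25% from none of them explicitly. What stands is that the trial was sized on having COVID-19, without restriction to PCR-confirmed cases.

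**Conclusion.** The contradiction holds on the text alone and concerns the primary endpoint, so it should be corrected before analysis. As written, the analysis entry replaces acquisition of infection by symptom-triggered, PCR-positive disease.

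The size of the harm rests on assumed detection shares. With no true effect, the chance of a result favouring the spray would be about 8% to 26% in the two scenarios shown, against 2.5%. The 80% power was computed for having COVID-19 and is not established for PCR alone: about 69% to 46% if an equal 20% to 50% of cases were missed, or 83% to 89% in the two scenarios with lower detection on the spray, where the test answers a different question. None of these figures is a prediction for this trial.

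**What to change.** Replace the first sentence of the Primary outcome entry under Statistical analysis with a definition that matches Outcomes, for example: *the primary outcome is binary, a case being PCR-confirmed infection or seroconversion from a negative baseline sample to a positive exit sample.* Apply the chi-square test, odds ratio and logistic model to that variable.

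Report PCR-positive disease and seroconversion separately as supportive analyses, so that a reader can see whether a difference lies in infection or in its detection.

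A participant with no positive PCR and no exit serology has an undetermined composite outcome. Do not count that person as a confirmed non-case; handle the record under the missing-data provision already in the Statistical analysis section.

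The cost is a sentence or two. Entry and exit serology are already planned, no further data are needed, and 304 evaluable (380 recruited) stays valid under the plan's own assumed rates.
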